## Introduction

Traumatic brain injury (TBI) is one of the main leading causes of death and lifelong disability in the world. One of the most important neurological consequences following TBI is the development of post traumatic epilepsy (PTE), which is responsible for approximately 5% of all focal epilepsy etiologies in the general population [1]. TBI patients present a higher risk to develop epilepsy than the general population, with 10–20% cumulative probability in 5 years [2–4]. The type and severity of injury correlates with the likelihood for a person to develop epilepsy, varying from 2.9% for moderate TBI to 17–27% for those who had severe TBI [2, 5–7]. Importantly, risk of epilepsy reaches 50% for patients with penetrating head injury [8]. Besides the high incidence, the causative links between TBI and epilepsy are still not completely understood, and there is currently no clinically available treatment or strategy that influences the likelihood of PTE development after brain injury [9].

Preclinical studies showed that anticholinergic drugs have the potential to modify neural plastic processes hampering epileptogenesis in animal models of epilepsy [10]. Among these drugs, biperiden, a cholinergic antagonist acting in the muscarinic receptor, administered soon after brain injury, delayed the latency and decreased the incidence and intensity of spontaneous seizures after brain injury [11]. These results were recently corroborated by other groups [12].

As a subsequent step, the use of biperiden in the acute phase after brain injury showed to be safe in a small phase II clinical study, which also served to test the feasibility of an interventional and prospective trial [10]. Here, the present Phase III study was designed to evaluate the safety and efficacy of biperiden in preventing the development of PTE in adult patients, who have suffered moderate or severe TBI, in a larger multicenter prospective study. Other clinically relevant neurological outcomes due biperiden treatment will also be investigated. The aim of this study is to evaluate the efficacy and safety of biperiden in preventing the development of epilepsy in patients that suffered TBI.

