### Randomization and allocation concealment

Patients will be randomly assigned to receive placebo or biperiden using a random table generated by STATA® v17 software, in a 1:1 rate, in random permuted blocks and considering the recruiting centers as a criterion for stratification. The allocation concealment will be assured using the REDCap (Research Electronic Data Capture), a web-based software platform [16, 17].

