### Statistical analysis

The statistic plan followed the Guidelines for the Content of Statistical Analysis Plan in Clinical Trials [20].

Sample size calculation was performed based on previous studies [1, 2, 5–8, 10, 21] using the Pocock formula [22]. Assuming a difference in reduction of PTE of 15% between the placebo and biperiden groups at 24 months, type 1 error (alpha) of 0,05 and type 2 error (beta) of 0.10 and 20% dropout rate, 156 patients per group would be required to provide 90% power with 5% level of significance. According to epidemiological data provided by a pilot study [10], we estimated that the inclusion pace could be 3–5 patients/center/month leading to study completion within 42 months.

The hypothesis used in the analysis is that biperiden is superior to placebo. All patients who receive at least one dose of randomized study drug will be included into the safety analysis and all patients who receive at least one dose of a randomized study drug and who has an evaluable follow-up data will be included in intention-to-treat analysis. Missing data will be handled by chained-equation multiple imputation methods considering relevant baseline and outcome variables. A complete case analysis will be presented as a sensitivity analysis.

We plan to analyze the primary outcome using logistic regression, adjusting for age and sex at baseline. The result of this regression will be an odds ratio representing the relative effect of the intervention compared to the placebo. Secondary outcomes will be analyzed using appropriate generalized linear models, including logistic and linear models. Planned subgroups include type of epileptic seizures and the presence of the polymorphic ε4 allele of the apolipoprotein E gene (Table 1).

An interim analysis will be performed at 50% recruitment considering the primary outcomes. At the interim enrollment point, the DMC will consider as criteria for early interruption of the study p<0.001 for safety and p<0.0001 for efficacy analysis. The Pocock [22] stopping boundaries, will be used as a reference rather than as a rigid rule. In addition, the DMC will also consider the effect on other secondary outcomes, in the occurrence of unpredicted adverse events and external new evidence available during trial conduction.

A confidence level of 95% will be assumed for all analyses that will be conducted using Stata v17.

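### Agreement between multiple imputation and complete case would not show that the result survives outcome-related dropout; a tipping-point analysis would

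*Protocol article*

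**What the plan says.** All the relevant text is in the protocol article, under Statistical analysis.

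- Main handling of missing data: "Missing data will be handled by chained-equation multiple imputation methods considering relevant baseline and outcome variables".
- The check on it: "A complete case analysis will be presented as a sensitivity analysis". The article names no other sensitivity analysis for missing data.
- Planning values: "type 1 error (alpha) of 0,05 and type 2 error (beta) of 0.10 and 20% dropout rate", with "156 patients per group would be required to provide 90% power with 5% level of significance".
- The primary outcome (any unprovoked seizure from day 7 to 24 months) is analysed by logistic regression adjusted for age and sex.
- The intention-to-treat set is limited to dosed patients who have usable follow-up, so a patient with none enters neither the imputed nor the complete-case analysis.

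**The concern.** A sensitivity analysis is most useful when it relaxes the assumption that carries the main result. Chained-equation imputation, as normally run, assumes that loss is unrelated to the missing PTE status once the variables in the imputation model are known (missing at random). Complete-case logistic regression needs a similar condition given treatment, age and sex. Neither covers a patient who is lost because of a seizure nobody recorded, or lost for reasons that track seizure risk beyond what was measured.

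If such loss differs between arms, both analyses can be biased in the same direction. A report that they agree could then be read as showing that dropout does not matter. Two years of follow-up after severe injury, with seizures captured by diary, visit or telephone, makes outcome-related loss plausible, though the article does not say that it is expected.

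**Working it through.** **Step 1. The plan's own figure, and how much could be missing.** The article gives the difference ("Assuming a difference in reduction of PTE of 15% between the placebo and biperiden groups at 24 months") but not the arm rates. I assume 25% versus 10%, two-sided alpha 0.05 and 90% power. The placebo rate is within the severe-injury range in the Introduction ("varying from 2.9% for moderate TBI to 17–27% for those who had severe TBI").

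n = [p1(1−p1) + p2(1−p2)] × (z₀.₉₇₅ + z₀.₉₀)² / (p1−p2)² = (0.1875 + 0.09) × 10.507 / 0.0225 = 129.6, so 130 per arm. Then 130 × 1.2 = 156, the stated figure.

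Twenty per cent of 156 is 31.2, so about 31 missing and 125 observed per arm. That is an upper figure. Inflating by 1.2 leaves 156 − 130 = 26, and patients without usable follow-up are outside the analysis set.

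**Step 2. What outcome-related loss does to complete case.** For a binary outcome:

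observed OR = true OR × [P(seen | PTE) / P(seen | no PTE)] in the biperiden arm ÷ the same ratio in the placebo arm.

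Take no true effect and 20% placebo loss regardless of outcome, so the placebo ratio is 1. The loss rates are assumed.

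- Biperiden loses 40% of patients with PTE and 13% without: 0.60/0.87 = 0.69, log OR −0.37.
- Biperiden loses 50% with and 12.5% without: 0.50/0.875 = 0.57, log OR −0.56.

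**Step 3. Does imputation correct it?** Simulated trials, 156 per arm, about 20% missing, no true effect:

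| Loss in biperiden arm (with / without PTE) | Imputation uses | Complete case | Imputation | Same verdict |
|---|---|---|---|---|
| 40% / 13% | age, sex | mean log OR about −0.37; 22% false positive | about −0.37; 21% | 99% |
| 50% / 12.5% | adds a marker, OR 3 with PTE | −0.60; 39% | −0.57; 37% | 93% |
| 50% / 12.5% | adds a marker, OR 6 with PTE | −0.55; 34% | −0.48; 28% | 93% |

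A further run with outcome-related loss gave −0.48 (29% false positive) for complete case and −0.35 (18%) for imputation. The methods separated more there, but both remained biased.

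**Step 4. When the comparison does work.** Suppose loss in the biperiden arm depends only on a measured interim marker: present in 60% of PTE and 10% of non-PTE patients, with loss of 50% if present and 11% if absent. Then P(seen | PTE) = 1 − (0.6×0.50 + 0.4×0.11) = 0.656 and P(seen | no PTE) = 1 − (0.1×0.50 + 0.9×0.11) = 0.851. The ratio is 0.77, log OR −0.26. In simulation, complete case gave −0.25 with 12% false positives. Imputation using the marker gave 0.00 with 5%, and verdicts agreed in 87% of trials. Here the gap is a real warning.

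**Step 5. How far a result could move.** Pooled two-proportion z-test; placebo dropouts are held at the observed placebo rate (31/125 = 24.8%, so 38.7 of 156).

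*Borderline result, 31/125 versus 18/125:* z = 0.104/0.0502 = 2.07, p = 0.038. Biperiden events become 18 + 31r:

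- r = 0.14 (about the observed biperiden rate): p = 0.020
- r = 0.20: p = 0.041
- r = 0.25 (about the placebo rate): 25.75 of 156, p = 0.070
- r = 0.30: p = 0.114

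*Planned effect, 31/125 versus 12/125:* p = 0.0015. Missing at random implies about 31 × 0.096 = 3 events among the missing. With 12 events p = 0.038; with 13 of 31 (42%) p = 0.055. Allowing for imputation uncertainty also puts the tipping point at 13. Across assumed placebo rates of 20–30% it is 13 to 14. In the extreme cases the difference runs from (31 − 43)/156 = −7.7 points to (62 − 12)/156 = +32.1 points.

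The z-tests that fill in outcomes treat them as observed, so their p-values are somewhat too small. That is why r = 0.14 gives 0.020 rather than 0.038.

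**The case against.** The strongest reply has four parts.

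**The comparison is not empty.** A reader might infer that complete case is uninformative by construction and must agree with the imputation whether or not its assumption holds. The article does not support that: it imputes from outcome variables as well as baseline ones, and EEG, mRS and seizure status are collected at seven visits. Step 4 shows that the two can part. This objection stands, and it is the reason to keep complete case.

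**Other checks may exist.** A reader might also infer that no other sensitivity analysis is planned. The article is condensed, says only that complete case is *a* sensitivity analysis, and its SAP is not shown. So the point is limited to the check the article names and what that check can show.

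**The amount of missing data is uncertain.** The 20% is a planning allowance. The outcome is cumulative, so a patient with a confirmed seizure before dropping out already counts as an event. Telephone contact and repeated attempts reduce loss, and with blinding and only ten days of treatment the article gives no reason for strongly arm-specific loss. All fair: 31 per arm is an upper figure and the loss rates in Steps 2 to 4 are illustrations. None of this tests the assumption for the patients who remain missing.

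**The borderline example is chosen.** It is. A result at p = 0.04 is easily overturned, whereas the planned effect is fairly robust. Both must be shown together.

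**Conclusion.** The point holds in a limited form. Complete case beside imputation can detect loss related to measured variables that the imputation uses. It cannot show whether the conclusion survives loss related to unseen PTE, and agreement between the two should not be reported as if it did.

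The practical size depends on the result. With 31 missing per arm, a barely significant difference is lost if missing biperiden patients merely have the placebo rate. A difference near the planned 15 points is lost only if about 42% of them have PTE, against about 10% expected under missing at random. These figures rest on assumed arm rates, a two-sided test and full 20% missingness within the analysis set. The false-positive rates rest further on assumed loss patterns and are not forecasts for this trial.

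The primary analysis and the sample size are not in question. This is a cheap improvement.

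**What to change.** Keep the complete-case analysis as a secondary display, and add a prespecified analysis before unblinding. Possible wording:

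*The planned imputation will be repeated with the log-odds of PTE among patients with missing outcome shifted by arm over a stated range, including the case in which missing biperiden patients take the placebo rate. The shift at which the conclusion changes will be reported. Complete case will also be shown; its agreement with the main analysis will not be taken as evidence against outcome-related loss.*

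If the SAP already contains such an analysis, a sentence pointing to it is enough.

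Cost: a few more runs of an imputation already planned in Stata and one short paragraph. Sample size, conduct and primary analysis stay as they are. The downside is that the result may look less robust.

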### Participants

The study will enroll adults (18 to 75 years) of both sex who fulfill the following inclusion criteria: meet the moderate or severe TBI criteria according with the Glasgow Coma Scale (GCS) [15], in such a way that GCS is between 6 and 12 at the accident scene and/or between 3 (if sedated) and 12 at hospital admission; have computerized tomography (CT) scan with evidence of acute intraparenchymal hemorrhage and/or contusion; able to receive the first dose of treatment or placebo within 12 hours of brain injury, regardless of the accident cause. Participants, or their relatives in the event of patient´s unconsciousness, will have to provide written informed consent within 48 hours from the beginning of the protocol. Exclusion criteria are: current use of biperiden or antiseizure drugs; history of epilepsy, presence of other conditions that could increase risk factors for epilepsy development, such as perinatal injuries, meningitis, encephalitis, neoplasia, acute stroke, neurodegenerative diseases; any condition precluding the use of biperiden such as pregnancy, glaucoma, benign prostatic hyperplasia, atrioventricular block or cardiac arrhythmias; megacolon or mechanical obstruction of the gastrointestinal tract and inability to perform follow-up visits (e.g. homeless patients); refusal to participate in the study and current enrollment in other clinical trial. Alcohol intoxication or other psychotropic drug use at hospital admission will not lead to protocol exclusion.

We intend to recruit participants with acute TBI from at least ten hospitals located at different regions from Brazil (North, South, Southeast, Midwest and Northeast). After a first screening at the emergency care unit (ECU) for confirming eligibility criteria (which requires standard CT scan for acute TBI cases, electrocardiogram and pregnancy test for safety), those who fulfill all criteria will be included in the study. Because the emergency scenario and the injury severity, when the participant is not able to inform his medical history and is not accompanied by an appropriate informant, consent to participate and exclusion criteria might be confirmed within two days of protocol beginning. Participants will be prospectively monitored at their respective neurology/neurosurgery centers.

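### The primary model adjusts only for age and sex, omitting centre (the randomisation stratum) and GCS-based severity; the test stays valid but gives up modest precision

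*Protocol article*

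**What the plan says.** The Statistical analysis section fixes the primary model: "We plan to analyze the primary outcome using logistic regression, adjusting for age and sex at baseline". The covariate set is stated outright, so it is not a detail left to a later analysis plan.

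Other sections bear on that choice:

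- Randomization and allocation concealment: allocation is "in a 1:1 rate, in random permuted blocks and considering the recruiting centers as a criterion for stratification".
- Participants: "We intend to recruit participants with acute TBI from at least ten hospitals". Eligibility requires that "GCS is between 6 and 12 at the accident scene and/or between 3 (if sedated) and 12 at hospital admission", so GCS in at least one of the two settings is assessed for entry.
- Introduction: PTE risk depends on severity, "varying from 2.9% for moderate TBI to 17–27% for those who had severe TBI". It also says that "risk of epilepsy reaches 50% for patients with penetrating head injury".

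Severity is neither a stratification factor nor among the subgroups in Table 1. The article gives no reason for choosing age and sex or for omitting centre and severity.

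**The concern.** Two separate things are left out.

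**Centre.** Stratified blocks balance the arms within each centre. If PTE risk varies between centres, that balance makes the treatment comparison more precise than a model without centre recognises. The standard error is then too large and the test conservative.

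**Severity.** By the article's own figures severity is a strong predictor of PTE. Nothing in the design balances it beyond chance, and nothing in the analysis corrects it. An imbalance that arises by chance passes into the treatment estimate, and the precision available from a prognostic covariate is not used. If severity turns out visibly unbalanced, an adjustment chosen at that stage will look data-driven.

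Events are few and take two years to observe, so precision obtainable from data assessed at entry is worth having.

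**Working it through.** **1. The plan's own sample size.** The article gives a 15% difference, alpha 0.05, beta 0.10, 20% dropout and 156 per group, but no control rate. With an assumed 25% versus 10% and the two-sided unpooled formula:

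n = (1.96 + 1.2816)² × (0.25×0.75 + 0.10×0.90) / 0.15² = 10.51 × 0.2775 / 0.0225 ≈ 130 per arm, and 130 × 1.2 = 156.

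This matches exactly, but other assumed rates come within 3%, so 25% versus 10% is a working assumption. Losing 20% of 156 leaves about 125 per arm and 125 × (0.25 + 0.10) ≈ 44 events.

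**2. Strength of the severity gradient.** Risk ratios are 17/2.9 = 5.9 and 27/2.9 = 9.3. Odds ratios are (0.17/0.83)/(0.029/0.971) ≈ 6.9 and (0.27/0.73)/(0.029/0.971) ≈ 12.4.

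**3. What a chance imbalance can do.** With 125 per arm and half the patients severe (assumed), the arm difference in severe share has SD √(2 × 0.25/125) = 0.063, so its 95% range is ±1.96 × 0.063 ≈ ±12 points. An imbalance of that size shifts the PTE difference by 0.124 × (0.17 − 0.029) = 1.7 points to 0.124 × (0.27 − 0.029) = 3.0 points, against the planned 15.

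**4. Power and type I error by simulation.** Settings: 10 centres, 130 evaluable per arm balanced within centre, overall rates 25% versus 10%, 60% severe, 4,000 trials per cell, two-sided Wald test. The between-centre SD on the logit scale (0, 0.5, 1.0) is assumed; the article gives none. Centre was fitted as fixed indicators. Monte Carlo standard error is about √(0.9 × 0.1/4000) = 0.5 point for power and √(0.05 × 0.95/4000) = 0.3 point for type I error.

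| Severity OR | Centre SD | Power: age+sex | + GCS | + centre | + both | Type I: age+sex | Type I: + both |
|---|---|---|---|---|---|---|---|
| 7 | 0 | 89.6% | 91.8% | 90.3% | 92.2% | 5.7% | 6.3% |
| 7 | 0.5 | 89.9% | 91.7% | 91.0% | 92.8% | 4.7% | 5.4% |
| 7 | 1.0 | 90.2% | 91.4% | 92.0% | 93.6% | 3.7% | 4.9% |
| 12 | 0 | 89.4% | 91.8% | 90.0% | 92.3% | 4.6% | 5.4% |
| 12 | 0.5 | 90.2% | 92.8% | 91.1% | 93.8% | 5.1% | 6.1% |
| 12 | 1.0 | 90.0% | 92.8% | 92.2% | 94.8% | 4.0% | 5.8% |

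The gain from both additions runs from 92.2 − 89.6 = 2.6 to 94.8 − 90.0 = 4.8 points. Severity alone adds 1.2 to 2.8 points. Centre alone adds about 1 point or less at SD 0 to 0.5 and about 2 points at SD 1.0. Some of the gain with fixed centre indicators comes with a type I error up to about 6%, so not all of it is real.

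**5. Error given an imbalance.** In the 9–11% of null trials where the severe share differed by more than 10 points between arms, the age-and-sex model rejected 7–11% of the time. Adding GCS brought this to 3–6%.

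**The case against.** The strongest reply is that nothing in the plan is invalid. The model is prespecified, randomisation protects the comparison, and the confidence interval already allows for chance imbalance. This stands. A reader might infer that leaving out severity biases the result, or that ignoring the stratum invalidates the test. The figures do not support either: unconditional type I error for the age-and-sex model is 4.6–5.7% at centre SD 0 to 0.5 and about 4% at SD 1.0, which is conservative. The 7–11% rejection rate applies only to trials already selected for imbalance.

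A second reply is that the size rests on assumptions. This also stands:

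- The centre contribution is material only if centres differ strongly, which the article does not show.
- The simulation keeps the article's severity odds ratio but not its absolute risks. With 60% severe and 25% overall, an odds ratio of 7 implies about 7.6% and 36.6% (0.4 × 7.6 + 0.6 × 36.6 = 25.0), which exceeds 17–27% for severe TBI. Reaching 25% from 2.9% and 27% would need (0.25 − 0.029)/(0.27 − 0.029) = 92% severe, and the gain would then be smaller because nearly everyone falls in one category.
- The Introduction's figures describe TBI in general. The trial also requires haemorrhage or contusion on CT, so the gradient may differ here.

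A third reply is that GCS is not one uniform covariate: it comes from the scene, from admission, or both, and sedation affects it. That is a reason to define it in advance, not to omit it.

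It is also tempting to call severity the strongest known predictor. The Introduction does not support that, since it gives 50% for penetrating injury.

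**Conclusion.** The point holds as one of precision and of error conditional on imbalance. It is not one of systematic bias or inflated overall error. The stated covariate set is poorly chosen: it leaves out the only stratification factor the article names and a variable that the article itself presents as strongly related to PTE and assesses for entry.

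The loss is modest: about 2.5 to 5 points of power for both omissions together, assuming 25% versus 10%, 60% severe and 10 centres, and mostly due to severity unless centres differ strongly. A reader might infer that the trial is underpowered because of this model. It is not: under the same assumptions the planned model has 89–90% power, in line with the stated 90%. The change is worth making because it costs little and settles in advance how severity is handled.

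**What to change.** Before unblinding, prespecify the primary logistic model with treatment, age, sex, GCS severity category and centre.

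- **Severity.** Define one rule for the covariate. For example: moderate versus severe from hospital-admission GCS, using scene GCS where the patient was sedated or the admission value is missing.
- **Centre.** Fit it as a random intercept. About 44 events over ten or more centres is roughly four per centre, too few for fixed effects, and fixed indicators took type I error to about 6% in the simulation. The random-intercept version was not simulated, so its operating characteristics should be checked before it is adopted. Replacing centre with geographical region would not match the randomisation stratum.
- **Imputation.** Include the same variables in the chained-equation imputation model.

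Cost: a short change of text, no extra patients and no new assessments, provided both GCS values and sedation status are recorded. Fitting becomes slightly more complex, particularly when a mixed model is combined with multiple imputation. The reported odds ratio becomes conditional on the added covariates and will differ from one adjusted for age and sex only, so the report should say so.

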### Interventions

Within 12 h after TBI, participants will receive intravenous (i.v.) infusions of 5 mg of biperiden (1 mL; Cinetol, Cristália, Brazil) diluted in 100 mL of 0.9% saline (treatment group) or 1 mL of sterile vehicle (sodium lactate, lactic acid, sodium hydroxide and water for injections) diluted in 100 mL of 0,9% saline (placebo group), every 6 hours for 10 days after TBI, until completing 40 total doses.

Patients will receive all standard of care treatment indicated for their clinical condition according to the hospital protocol and will not be deprived of any other required treatment, including all types of anti-seizure drugs, because of their participation in this study, regardless of the randomization group (placebo or biperiden) or the protocol period (intervention or follow up). Patients can be discontinued from the protocol if they remove the consent to participate; in any health conditions that health care providers, with sponsor agreement, believe that it is to the advantage of the patient not to comply with the procedures specified in this protocol; in case of screening error when including patients with history of epilepsy predicted in the study exclusion criteria (when this finding cannot occur at the time of recruitment).

During the hospitalization period, blood samples will be collected to analyze the genetic profile of patients regarding the presence of the polymorphic ε4 allele of the apolipoprotein E gene (APOEε4). Laboratory analyses will be performed by a central laboratory (DASA, São Paulo, Brazil), which is accredited by the College of American Pathologists (CAP, Northfield, IL, USA). Additional patients’ information, such as occurrence of adverse events, sociodemographic data, occurrence of symptomatic acute seizures, unprovoked epileptic seizures starting 7 days after TBI and clinical evolution will be collected during the hospitalization period. Suspected and diagnosed severe adverse events will be reviewed and adjudicated by the Ethics Committee and the external Data Monitoring Committee.

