**Other Outcomes**		
Mortality incidence	Number of participants that evolved to death (all cause mortality)	24
Non-serious adverse events occurrence	Number of participants experiencing at least one non-serious adverse event	1, 3, 6, 9, 12, 18, 24
**Subgroup analysis**	Age, gender, region of lesion, occurrence of SAS, frequency and type of epileptic seizures, presence of APOEε4, educational level.	

The data analysis is based on comparisons between biperiden x placebo groups considering the end of follow up or run-in periods. PTE post-traumatic epilepsy; EEG electroencephalography; mRS modified Rankin scale. SAS symptomatic acute seizures; APOEε4 polymorphic ε4 allele of the apolipoprotein E gene.

As primary outcome, we will investigate the number of participants with unprovoked seizures, counted starting 7 days after TBI until the two years follow-up period. The presence of seizures will be clinically confirmed by a neurologist to indicate PTE. Also, as a primary outcome, the number of patients experiencing at least one serious adverse event in the two years follow-up period will be compared between placebo and biperiden groups. The ICH Guideline for Clinical Safety Data Management: Definitions and Standards for Expedited Reporting defines serious adverse event as: “A serious adverse event (experience) or reaction is any untoward medical occurrence that at any dose: results in death, is life-threatening (NOTE: The term "life-threatening" in the definition of "serious" refers to an event in which the patient was at risk of death at the time of the event; it does not refer to an event which hypothetically might have caused death if it were more severe); requires inpatient hospitalization or prolongation of existing hospitalization, results in persistent or significant disability/incapacity, or is a congenital anomaly/birth defect” [19].

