For secondary outcomes, it will be considered the frequency and type of clinical seizures at each specific timepoint during the two years follow up. Also, the number of participants presenting epileptiform discharges and electrographic seizures on the electroencephalogram recording will also be analyzed. For the neuropsychological status participants will be categorized according to the specific percentile rank defined for each cited standard test. Five health-related quality of life domains (mobility, usual care, usual activities, pain/discomfort, anxiety/depression) will be covered and compared between groups according to specific and total scores.

Other outcomes include the mortality incidence and occurrence of non-serious adverse events during the two year protocol.

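### Seizure type and frequency are listed as subgroups although they are part of the primary outcome, and acute seizures are listed as a subgroup although most of their window probably falls after dosing starts

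*Protocol article*

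**What the plan says.** The protocol article names subgroups in two places.

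- **Statistical analysis:** "Planned subgroups include type of epileptic seizures and the presence of the polymorphic ε4 allele". The sentence then refers the reader to Table 1.
- **Table 1, subgroup row:** "Age, gender, region of lesion, occurrence of SAS, frequency and type of epileptic seizures, presence of APOEε4, educational level". The note under the table says that the analysis compares biperiden with placebo.

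Four other statements fix what these variables are.

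- **Primary efficacy outcome (Outcomes):** "we will investigate the number of participants with unprovoked seizures, counted starting 7 days after TBI until the two years follow-up period". It is analysed by logistic regression and reported as an odds ratio.
- **Secondary outcomes (Outcomes):** "it will be considered the frequency and type of clinical seizures at each specific timepoint during the two years follow up". The variables in the subgroup row are thus already outcomes.
- **Exclusion criteria (Participants):** these include "current use of biperiden or antiseizure drugs; history of epilepsy".
- **Treatment (Interventions):** "Within 12 h after TBI, participants will receive intravenous (i.v.) infusions of 5 mg of biperiden", repeated every 6 hours for 10 days. SAS and unprovoked seizures from day 7 are recorded as separate items during the hospital stay.

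**The concern.** A subgroup analysis asks whether the treatment effect differs between kinds of patient who could be told apart before treatment. Randomisation protects that comparison only if membership of the subgroup cannot depend on treatment.

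Seizure type and frequency fail this test outright. A patient without a history of epilepsy has no epileptic seizure type to record until an unprovoked seizure occurs, and that seizure is the primary outcome. SAS may fail it too, because most of the acute period follows the first dose.

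At stake are one listed analysis that cannot return a result for PTE and another that could show an effect that is not there. The Discussion gives the search for patients who could benefit from prophylaxis as an aim. A variable known only after the outcome has happened cannot serve that aim.

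**Working it through.** The plan states no figure for its subgroups, so there is none to reproduce. The check is logic for seizure type and frequency, and timing plus an illustration for SAS.

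**1. Seizure type and frequency, with PTE as the outcome**

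Let Y = 1 if the patient has an unprovoked seizure between day 7 and 24 months.

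- In a stratum defined by any type, or any non-zero frequency, of unprovoked seizure, every patient has Y = 1. The rate is 100% against 100%. With a and c events and no non-events, the odds ratio is (a/0)/(c/0), which is undefined.
- In the stratum with no unprovoked seizure, every patient has Y = 0. The rate is 0% against 0% and the odds ratio is 0/0.
- A treatment-by-subgroup interaction compares these odds ratios, so it cannot be estimated either.

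This takes epileptic seizure to mean unprovoked seizure, as Table 1 implies by listing SAS separately.

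**2. Seizure type and frequency, with another outcome**

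For the modified Rankin Scale or quality of life, the strata can be compared. They still consist of patients selected by an event that the drug is meant to prevent. If the drug works, the patients who have seizures in the two arms are no longer alike.

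**3. SAS: timing**

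The article does not define the SAS window. Assume it ends where the counting of unprovoked seizures begins, at day 7.

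- Window: 7 × 24 = 168 h.
- Latest permitted first dose: 12 h.
- Part of the window after that dose: 168 − 12 = 156 h, and 156/168 = 93%.

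This is a share of time, not of events. Some SAS may occur before the first dose, but nothing in the article limits the subgroup to those.

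**4. SAS: possible size of the bias**

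Illustration with 2,000,000 simulated patients per scenario. All inputs are assumptions. An unmeasured severity U (standard normal) raises the risk of both SAS and PTE. Treatment T lowers SAS and does nothing to PTE:

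- logit P(SAS) = −1.5 + b·T + g·U
- logit P(PTE) = −1.4 + g·U

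| b | g | OR, all patients | SAS: placebo vs biperiden PTE (OR) | No SAS: placebo vs biperiden PTE (OR) |
|---|---|---|---|---|
| −0.7 | 1 | 0.995 | 35.1% vs 37.1% (1.09) | 20.5% vs 21.6% (1.07) |
| −0.7 | 2 | 1.000 | 56.8% vs 61.7% (1.23) | 19.1% vs 21.7% (1.18) |
| −1.4 | 1 | 1.002 | 35.0% vs 38.8% (1.18) | 20.4% vs 22.4% (1.13) |
| −1.4 | 2 | 1.002 | 57.0% vs 66.4% (1.50) | 19.0% vs 24.0% (1.35) |

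Among all randomised patients the null is recovered. Within both strata a false signal of harm appears, because the treated patients who still have SAS are more severe on average, and so are the treated patients who do not. If biperiden raised SAS, the direction would reverse. If it has no effect on SAS (b = 0), the strata stay balanced and there is no bias.

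**The case against.** **The subgroup row names no outcome.** It may loosely mean a breakdown of PTE by seizure type, or subgroups for other endpoints. This stands in part: the result that nothing can be estimated applies to PTE only. But the Statistical analysis section lists seizure type alongside APOEε4, a true baseline characteristic, and the note to Table 1 describes comparisons between arms. For other outcomes the selection problem in step 2 remains. If only a descriptive breakdown is meant, it belongs with the secondary outcomes, where the article already puts it.

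**The SAS bias is not established.** This stands. A reader might infer that an SAS subgroup is necessarily biased or bound to show harm. No section says that biperiden changes the risk of acute seizures, and the simulated odds ratios follow from chosen inputs. The documents support only that the subgroup is open to bias.

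**The analyses are exploratory.** This also stands. The abstract describes the search for factors that could influence results as exploratory. No stopping criterion is tied to a subgroup, and an analysis that returns no estimate would fail visibly.

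**Missing severity subgroup.** A reader might infer that leaving out baseline Glasgow Coma Scale severity is a further error. The Introduction says that both the type and the severity of injury relate to the risk of epilepsy, and its highest figure, 50%, is for penetrating injury. It does not rank severity first. The choice of baseline subgroups is the sponsor's.

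**Conclusion.** The point holds for the subgroup analyses and goes no further.

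- **Seizure type and frequency:** wrong as written. For PTE the within-stratum effect and the interaction cannot be estimated, whatever the event rates. For other outcomes the comparison conditions on an event after randomisation.
- **SAS:** conditionally at risk. Bias needs an effect of biperiden on acute seizures. Under the assumed inputs, the false odds ratios were 1.09 to 1.50 in patients with SAS and 1.07 to 1.35 in those without. The 93% share of the window rests on the assumption that SAS ends at day 7.

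The other five items (age, gender, region of lesion, APOEε4 and educational level) are baseline characteristics and are unaffected. A reader might infer that the main efficacy result is compromised. It is not: the primary logistic regression uses no seizure or SAS subgroup. This is a should-fix.

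**What to change.** 1. In the Statistical analysis section, remove seizure type from the planned subgroups.
2. In the subgroup row of Table 1, remove seizure frequency and type. Report them by arm as the secondary outcomes that the Outcomes section already names, with all patients analysed in the arm as denominator, so that the comparison is not confined to those who had seizures.
3. Report SAS by arm as an outcome. Table 1 does not now list it as one, so it needs a row.
4. Use SAS as a subgroup only for seizures before the first dose, and only where the time of the seizure relative to that dose is recorded.

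**Cost:** items 1 to 3 are wording changes, and SAS occurrence is already collected during the hospital stay. Item 4 depends on timing data. The article mentions collecting occurrence but does not say whether the time is recorded. If it is not, either a field must be added or the SAS subgroup dropped.
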